| - 1. Do you have any eye pain? | | 0 = No  1 = Yes |  | |  |
| - 1. If you do have eye pain, how often do you experience this? | | 0 = Never  1 = Once a week  2 = Once a day  3 = Several times a day  4 = Constantly |  | |  |
| - 1. Do you eyes water | | 0 = Never  1 = Occasionally  2 = Often |  | |  |
| - 1. During a typical day in the past week, how often did your eyes feel dry (so that you wanted to put water or other lubricant in them) | | 0 = Never 1 = Infrequently 2 = Frequently 3 = Constantly 4 = Not sure |  | |  |
| - 1. Do you epilate? | | 0 = No  1 = Yes |  | |  |
| - 1. How often do you epilate? | | 0 = Never  1 = More than once a week  2 = once/week to once/month  3 = Less than once a month |  | |  |
| - 1. When did you last epilate? | | 0 = Never  1 = Within last week  2 = 1 week to 1 month ago  3 = Greater than 1 month ago |  | |  |
| - 1. Who does the epilating? | | 0 = never  1 = You  2 = A friend or relative  3 = Health care worker |  | |  |
| - 1. What do you epilate with | | 0 = Don’t epilate  1 = Locally made forceps  2 = Machine made forceps  3 = Burning  4 = Cutting |  | |  |
| - 1. Has a health-worker previously told you that need eyelid surgery | | 0 = No  1 = Yes |  | |  |
| - 1. When was the last time you were offered surgery? | | 0 = Never  1 = Within last year  2 = >1 year ago |  | |  |
| - 1. If surgery has been recommended or offered to you in the past, but you have not received or accepted the surgery, what are your main reasons for this? *(list as many as appropriate)* | 0 = Never offered surgery (i.e. n/a) | | | *Yes No* | |
| 1 = No symptoms | | | *Yes No* | |
| 2 = Symptoms present, but didn’t know treatment needed | | | *Yes No* | |
| 3 = Cost | | | *Yes No* | |
| 4 = No one to accompany | | | *Yes No* | |
| 5 = Lack of time | | | *Yes No* | |
| 6 = Fear of the operation | | | *Yes No* | |
| 7 = Resistance of family | | | *Yes No* | |
| 8 = Transport difficulties | | | *Yes No* | |
| 9 = Don’t know where to get it | | | *Yes No* | |
| 10 = Other (specify reason) | | | *Yes No* | |
| Of the above reasons which is:   - 1. the most important*:* | |  | | | |
| - 1. the 2nd most important | |  | | | |

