Surgical complications such as granuloma, incomplete lid closure, inflammation from suture material and infection can occur. The clinical status of the eyelid at the suture removal (7-10 days) will be described. The risk of complications in the surgical arm of the trial will be calculated at one year and two years respectively. The risk of recurrence (defined as at least one lash touching the eyeball or clinical evidence of epilation or redo surgery) will also be estimated at each visit.

1. *Patient satisfaction*

Patients are asked the following questions on the follow up questionnaires that indicate their satisfaction with the procedure:

- 1. *Do you think your vision is worse, the same or better than before your surgery or epilation?*
  2. *Do you have eye pain?*
  3. *If you have eye pain is it worse, the same or better than before your surgery or epilation?*
  4. *Do your eyes water?*
  5. *If you had surgery, did you find it painful?*
  6. *If you have been epilating do you find it painful?*
  7. *If you had surgery and the eyelashes have returned, do you want to have further surgery?*
  8. *If you have been epilating would you prefer to have had surgery?*

1. The answers to each of these questions will be compared between the two arms of the trial at 12 months. Additionally the answers to questions (b) and (d) will be adjusted for baseline (pre-operative) response.

Footnotes

1. *Why is corneal opacification not the primary outcome measure?*

Although corneal opacification is the outcome that is responsible for blindness (rather than trichiasis which is a risk factor for this) it can not be used as a primary measure for the following reasons:

1. As few as 10% of patients will have corneal opacity at the outset of the study.
2. The rate of change of corneal opacity can be slow, and the clinical examination is not sensitive enough to detect very subtle changes
3. Corneal opacity can be caused by other insults such as infection and trauma.
4. *Why is visual acuity not the primary outcome measure*

As with corneal opacity, loss of visual acuity is the end stage process from the disease. However it can not be used as a primary outcome measure because it is affected by many other common conditions such as cataract, as well as simply by aging.

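### Five of the eight satisfaction questions apply only after a post-randomisation event, so comparing them between arms is not a randomised comparison

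*Protocol*

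**What the plan says.** The analytical plan for Trial 2, Secondary outcomes, Patient satisfaction, lists eight follow-up questions, (a) to (h), and gives one rule for all of them: "The answers to each of these questions will be compared between the two arms of the trial at 12 months". The only refinement is this: "Additionally the answers to questions (b) and (d) will be adjusted for baseline (pre-operative) response".

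Three questions are unconditional: (a) change in vision, (b) eye pain now, (d) watering. The other five open with a condition:

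- (c) "If you have eye pain is it worse, the same or better than before your surgery or epilation"
- (e) "If you had surgery, did you find it painful"
- (f) "If you have been epilating do you find it painful"
- (g) "If you had surgery and the eyelashes have returned, do you want to have further surgery"
- (h) "If you have been epilating would you prefer to have had surgery"

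At baseline, the Ophthalmic Questionnaire in Appendix B asks "Do you have any eye pain", with separate columns for the right and left eye. No visible section restricts the five conditional questions to description within a group or states their denominator.

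**The concern.** Randomisation makes the arms comparable as whole groups. It does not make comparable the subsets defined by what happened afterwards, and each of the five conditions arises afterwards: treatment received, continued epilation, recurrence, or pain at follow-up. A difference between arms on such a question mixes the effect of treatment with the effect of who qualifies to answer.

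The plan rejects this kind of contrast elsewhere. Its justification for modified intention to treat declines a per-protocol analysis of the primary outcome because a whole arm would be set against a selected part of the other.

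At stake is the reading of the patient-reported results. The Trial Follow-up Phase lists a questionnaire only at the one-year visit, so this is the one listed occasion for comparing them.

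**Working it through.** **Who answers each conditional question.**

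| Question | Condition | Surgery arm | Epilation arm | What the contrast becomes |
|---|---|---|---|---|
| (e) | had surgery | nearly everyone | only those operated on after randomisation | close to undefined |
| (g) | had surgery, lashes returned | those with recurrence | only those operated on, with recurrence | close to undefined |
| (f), (h) | epilating | those who took up epilation | those still epilating | two differently selected groups |
| (c) | pain at follow-up | those in pain | those in pain | selected by an outcome |

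Three sections of the analytical plan support these entries:

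- Participant flow, Censoring: a patient whose trial eye was operated on by another provider is a failure and is censored at once. The epilation arm therefore supplies few or no answers to (e) and (g).
- Justification of primary outcome measure: surgery-arm patients are expected to start epilating if their operation fails.
- Justification for using modified ITT: some epilation-arm patients stop because the lashes did not come back, and these are successes. They do not meet the condition for (f) and (h).

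**Plan's own figure.** The satisfaction section states none. The sample size section supplies the arm size: 1300 × 0.90 / 2 = 585. Its power also reproduces: Φ((0.10 − 0.05)/√((0.05×0.95 + 0.10×0.90)/585) − 1.96) = 90.3%, against 90% stated. Nothing below depends on that power.

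**Illustration for (c).** The protocol gives no pain rates, so these are assumptions. Suppose that (c) is answered only by those in pain, and let

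- A = 20%: pain under either treatment, of whom w_A = 50% say worse;
- E = 20%: pain only under epilation, of whom w_E = 10% say worse;
- 585 patients per arm.

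Over the whole arm, worse pain is

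- surgery: A·w_A = 0.20 × 0.50 = 10.0%;
- epilation: A·w_A + E·w_E = 0.10 + 0.20 × 0.10 = 12.0%;
- difference −2.0 points, favouring surgery.

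Among those who answer (c) it is

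- surgery: 0.10/0.20 = 50% of 117;
- epilation: 0.12/0.40 = 30% of 234;
- difference +20.0 points, favouring epilation; pooled two-proportion z = 3.67.

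**Range.** In general the whole-arm difference is −E·w_E, which is negative whenever w_E is above zero. The difference among responders is E(w_A − w_E)/(A + E), which is positive whenever w_E < w_A. With A = 20%, w_A = 50% and E from 5% to 30%:

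| w_E | Among responders (points) | Whole arm (points) | Reversal |
|---|---|---|---|
| 5% to 40% | +2 to +27 | −0.25 to −12 | yes |
| 50% | 0 | −2.5 to −15 | no, the difference vanishes |
| 60% | −2 to −6 | −3 to −18 | no |

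If surgery is also better within the always-in-pain group (45% against 50% worse; E = 20%, w_E = 10%), the whole-arm figures are 9.0% and 12.0%, while responders show 45% and 30% (z = 2.78). The direction still reverses.

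**The case against.** The strongest reply is that the follow-up form is not visible, so it is not established that pain-free patients leave the denominator of (c). On the baseline form, conditional items carry a zero code for people to whom they do not apply, including the item on frequency of eye pain. If the follow-up form does the same and those answers are kept, the comparison on (c) in the illustration is 10% against 12%, and the objection to (c) is largely met. This stands, and the point on (c) is conditional on it. It does not rescue (e) to (h): with non-applicable answers kept in, a contrast there would mainly restate which treatment people had.

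Second, (b) is compared in everyone and adjusted for baseline. In the illustration it reads 20% in pain on surgery against 40% on epilation, so a reader would see the benefit beside the odd result in (c). This softens the harm but does not make (c) a valid contrast.

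Third, the plan says only that answers are compared and names no test or model for these questions. Tabulation by arm would satisfy the sentence. That is fair, and the point is about the contrast, not about a wrong test.

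A reader might infer that all five comparisons can invert the truth. The documents do not support that. Reversal is shown for (c) alone, under assumed rates. For (e) and (g) there is almost nothing on one side, hence no direction to reverse. Nor are surgery-arm epilators simply failures: the plan counts them as successes if they keep lashes off the eye. Pain at follow-up may also be new rather than persisting.

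**Conclusion.** The point holds in limited form. The plan states a rule that covers all eight questions, and for five of them the people who qualify to answer are determined after randomisation. For (e) and (g) the contrast is close to undefined. For (f) and (h) it compares groups selected in different ways. For (c) it is selected if pain-free patients are left out, and it can then point the opposite way to the whole-arm comparison when the extra patients in pain in one arm are less likely to report worsening. The size for (c) rests wholly on assumed rates and on 585 answers per arm.

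It would go too far to infer that the trial's conclusion is at risk. Patient satisfaction is one of several secondary outcomes, and the primary non-inferiority comparison is untouched. The point is minor but cheap to correct.

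**What to change.** Replace the single rule with two:

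1. Compare between randomised arms, in everyone seen at 12 months, only (a), (b), (d) and one ordered pain outcome that combines (b) and (c): no pain, pain but better, pain the same, pain worse. Define it for the trial eye and adjust it for baseline pain, since the baseline item is recorded by eye.
2. Report (e) to (h) descriptively within the group to which each applies, with the denominator given and no comparison between arms.

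The cost is one paragraph, one derived variable and four fewer between-arm comparisons. The change uses questions already planned at baseline and follow-up. One limit remains: the combined outcome joins present pain with remembered change, which should be said when it is reported.

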**Summary of literature on non-inferiority for a binary outcome**

Rousson and Seifert (Biom J 2008 50(2)190-204

Let pI=proportion with outcome in intervention arm

pC=proportion with outcome in control arm

We can consider the difference of proportions D=pI-pc  or the odds ratio

The non-inferiority margin for D (ΔD) should depend on the value of pI.

The FDA (1997) recommend ΔD=0.1 if pI > 0.1

(ref: http://www.fda.gov/downloads/Drugs/GuidanceComplianceRegulatoryInformation/Guidances/UCM202140.pdf

If one uses odds ratios, the choice of Δ is independent of pI Several authors suggest an ΔOR = 0.5

**Sample size**

The formula for sample size per arm when the expected proportions with the outcome differ by arm is:

[figure not shown]

where

[figure not shown]
=proportion with outcome in control (surgery) arm

[figure not shown]
=proportion with outcome in intervention (epilation) arm

Δ = inferiority margin (value such that if the alternative hypothesis is true, the upper 95% CI for the difference in proportion failing will not exceed Δ with probability 1-
[figure not shown]

µ = expected difference in the treatment means (
[figure not shown]

β = power

α = 0.025 (
[figure not shown]

Supplement: Text S1 — Trial protocol. (DOC) [file pmed.1001136.s002.doc]
